## Abstract

**Background:**

We have developed a novel and brief semi-structured psychotherapeutic intervention for patients with advanced or metastatic cancer, called Managing Cancer And Living Meaningfully. We describe here the methodology of a randomized controlled trial to test the efficacy of this treatment to alleviate distress and promote well-being in this population.

**Methods/Design:**

The study is an unblinded randomized controlled trial with 2 conditions (intervention plus usual care versus usual care alone) and assessments at baseline, 3 and 6 months. The site is the Princess Margaret Cancer Centre, part of the University Health Network, in Toronto, Canada. Eligibility criteria include: ≥ 18 years of age; English fluency; no cognitive impairment; and diagnosis of advanced cancer. The 3–6 session intervention is manualized and allows for flexibility to meet individual patients’ needs. It is delivered over a 3–6 month period and provides reflective space for patients (and their primary caregivers) to address 4 main domains: symptom management and communication with health care providers; changes in self and relations with close others; sense of meaning and purpose; and the future and mortality. Usual care at the Princess Margaret Cancer Centre includes distress screening and referral as required to in-hospital psychosocial and palliative care services. The primary outcome is frequency of depressive symptoms and the primary endpoint is at 3 months. Secondary outcomes include diagnosis of major or minor depression, generalized anxiety, death anxiety, spiritual well-being, quality of life, demoralization, attachment security, posttraumatic growth, communication with partners, and satisfaction with clinical interactions.

**Discussion:**

Managing Cancer And Living Meaningfully has the potential to relieve distress and promote psychological well-being in patients with advanced cancer and their primary caregivers. This trial is being conducted to determine its benefit and inform its dissemination. The intervention has cross-national relevance and training workshops have been held thus far with clinicians from North and South America, Europe, the Middle East, Asia and Africa.

**Trial Registration:**

ClinicalTrials.gov NCT01506492 4 January 2012.

**Electronic supplementary material:**

The online version of this article (doi:10.1186/s13063-015-0811-1) contains supplementary material, which is available to authorized users.

## Background

Advanced or metastatic cancer is predictably associated with challenges and burdens that may lead to symptoms of depression and demoralization and fears of suffering, dependency, and mortality [1]. The multiple physical symptoms, the dramatic alteration in support needs and in personal relationships, the difficulty navigating a complex health care system, and the threat of impending mortality all may constitute pathways to distress in this population [2]. The challenge for individuals in this circumstance is to sustain a “double awareness” that allows them to remain engaged in life while facing the imminence of physical deterioration, shortened survival, and death [3]. A variety of individual and social factors may protect individuals in this circumstance, but professional support may also be of value to prevent and treat the distress that commonly emerges in this population [4].

Clinically significant depressive symptoms may be frequent in patients with advanced cancer and can be understood as a final common pathway of distress, emerging in response to the interaction of multiple disease-related, individual and psychosocial factors [1, 2, 5–7]. The most prominent of these are the physical burden of disease, attachment insecurity (i.e., worry about the availability of supportive relationships and the capacity to make use of them for emotional support), lower self-esteem, feelings of hopelessness and impaired spiritual well-being [1, 2]. Although many psychotherapeutic modalities have been used to treat depression (e.g., cognitive behavior therapy and interpersonal therapy), positive outcomes and sustained improvement may be most likely when treatment is directed at etiological and pathogenic factors that are specific to the context in which disturbances arise [8]. Preliminary findings in patients with advanced cancer also suggest that psychological treatments for depression are preferred over pharmacological ones [9], and that individual psychotherapy is preferred over group therapy because sessions can be flexibly tailored to patients’ individual needs, taking into account other clinic appointments and fluctuations in health status [10–13].

To address the relative lack of evidence-based individual therapies tailored for this population, we have developed a novel, brief, semi-structured, individual, manualized psychotherapeutic intervention to alleviate distress and promote well-being in patients with advanced or metastatic cancer. This psychotherapy, called Managing Cancer And Living Meaningfully (CALM) [4, 14, 15], addresses the specific problems and risk factors that contribute to the emergence of depressive symptoms in this circumstance [1, 2]. It shares features with manualized supportive-expressive [16–24], cognitive-existential [25, 26], and meaning-centered [27] group psychotherapies applied to patients with advanced and terminal disease. CALM provides support and reflective space for the processing of thoughts and emotions evoked by this traumatic condition and facilitates the resolution of practical and existential questions that face individuals with advanced disease. Such an intervention has the potential not only to relieve distress but also to promote psychological growth [28, 29]. The purpose of this phase III randomized controlled trial (RCT) is to evaluate the efficacy of the CALM intervention in patients with advanced cancer.

## Methods/Design

The study is an unblinded RCT with 2 trial conditions (intervention plus usual care versus usual care alone) and assessments at baseline, 3 and 6 months. The primary outcome is depressive symptoms as assessed by the Patient Health Questionnaire-9 (PHQ-9). The primary endpoint is at 3 months and the secondary endpoint is at 6 months. The site is the Princess Margaret Cancer Centre, part of the University Health Network and Canada’s largest comprehensive cancer treatment and research center where more than 10,000 patients are assessed annually and more than 1,000 patients attend outpatient clinics daily [30]. The phase III protocol and related documents were approved by the Research Ethics Board (REB) of the University Health Network on 5 February 2010 (UHN REB #09-0855-C). A number of subsequent amendments to allow a phase IIA non-randomized and a phase IIB randomized pilot were approved by the REB prior to the final amendment and launch of this phase III trial in January 2012. Patients are recruited from eight approved tumor sites: gastrointestinal, lung, gynecological, breast, genitourinary, sarcoma, melanoma and endocrine. Patients are approved for trial enrollment by the principal investigators (GR, SH, CL) prior to randomization.

### Inclusion/Exclusion Criteria

The inclusion criteria are: 1) ≥ 18 years of age; 2) fluency in English; 3) no cognitive impairment indicated in the medical record or by the attending oncologist; and 4) a confirmed diagnosis of stage III or IV lung cancer, any stage of pancreatic cancer (due to the aggressiveness of this disease), unresectable cholangiocarcinoma, unresectable liver cancer, unresectable ampullary or peri-ampullary cancer or other stage IV (metastatic) gastrointestinal cancer, stage III or IV ovarian and fallopian tube cancers, or other stage IV gynecological cancer; and stage IV breast, genitourinary, sarcoma, melanoma, or endocrine cancers (all of the above with expected survival of 12–18 months). Patients meeting inclusion criteria undergo a brief interview with a research staff member to identify the following exclusion criteria: 1) major communication difficulties; 2) inability to commit to the required 3–6 psychotherapy sessions (i.e., too ill to participate, lack of transportation, insufficient motivation due to lack of distress); 3) cognitive impairment as indicated by a score < 20 on the Short Orientation-Memory-Concentration (SOMC) test [31], unless deemed suitable at the recruiter’s discretion, or due to brain metastases; 4) actively receiving psychiatric or psychological intervention in the Department of Supportive Care (formerly the Department of Psychosocial Oncology and Palliative Care) at the Princess Margaret Cancer Centre at the time of study approach; 5) refusal to accept randomization; and 6) prior treatment with CALM therapy during an earlier phase of the study.

### Procedure

Research staff screen the outpatient oncology clinic lists of eight solid tumor sites on a daily basis. Patients with advanced cancer are identified and mailed introductory letters concerning the study. These patients are approached by research staff for study recruitment while attending clinic appointments. During the recruitment process, the study design and intervention are described to patients and the inclusion/exclusion criteria are reviewed. Participants are also informed at study recruitment that if they are not randomized to receive CALM therapy, they will be offered the opportunity to receive CALM after completion of the final 6-month assessment. After providing written informed consent, cognitive functioning and other exclusion criteria are assessed, medical and demographic information is collected, baseline measures are administered, a diagnostic interview for depression is conducted, and eligible patients are randomized. Some patients who screen fail may be eligible for reapproach at a later date.

### Trial conditions

Participants in the intervention group receive usual care plus CALM, a semi-structured psychotherapy designed for patients with advanced cancer. CALM was developed based on empirical data, clinical observations, and the theoretical foundations of relational [32], attachment [33] and existential [34] theory.

CALM includes 3–6 individual psychotherapy sessions, each approximately 45–60 minutes in length, delivered over 3-6 months. The sessions cover 4 domains: 1) symptom management and communication with health care providers; 2) changes in self and relations with close others; 3) sense of meaning and purpose; and 4) the future and mortality [14, 15]. All domains are addressed with each patient, but the time devoted to each and the sequence in which they are addressed is based on the salience of concerns for each patient during the session. Therapists aim to deliver at least 3 sessions within 3 months. Non-compliance with intervention is defined as having less than 3 sessions over the course of the trial.

CALM is delivered by specially trained therapists, primarily master's level social workers, in the Department of Supportive Care at the Princess Margaret Cancer Centre. Therapists are trained and supervised by the clinician investigators who developed the intervention (GR, SH). The participant’s primary caregiver (e.g., spouse/partner, adult son/daughter, family member), or significant other, is invited to participate in one or more of the therapy sessions, when acceptable to the patient.

At any time during the intervention, patients considered by the therapist to be at acute risk for suicide, or who demonstrate significant worsening of depression or other psychiatric co-morbidities that require treatment, will be referred for psychiatric assessment and treatment in the Department of Supportive Care. This may include pharmacotherapy or other psychiatric interventions.

Participants in the control group receive usual care alone. At the Princess Margaret Cancer Centre this includes routine treatment and follow-up in medical, surgical and/or radiation outpatient oncology clinics, as well as a clinic-based distress screening program, referred to as DART (Distress Assessment and Response Tool) [35], with results provided at the time of the clinic visit to oncology clinic staff. Clinic staff may refer any patient for specialized psychosocial oncology services (provided by trained volunteers and by social work, psychiatry and psychology staff) or to palliative care, based on clinical judgment, patient requests and/or distress screening scores. In the event that a usual care participant reports suicidal intent, the principal investigators are contacted and the patient is assessed by a psychiatrist from the Department of Supportive Care.

Approximately one third of patients with metastatic cancer are referred for psychosocial care at the Princess Margaret, two thirds of whom are seen by a social worker [36]. Approximately 65 % of social work consultations involve provision of practical or instrumental care (e.g., urgent drug coverage, referral for admission to the Acute Palliative Care Unit, complex continuing care placement, etc.); 35 % of consultations involve brief supportive interactions to alleviate emotional distress in patients and/or family members. Control participants do not typically receive structured counseling from social work as part of usual care. Of those referred to psychiatry or psychology, less than one third receive a structured or semi-structured psychotherapy. Overall, less than 10 % of patients with metastatic cancer at the Princess Margaret Cancer Centre receive any form of semi-structured psychotherapy that is similar to CALM therapy. To avoid contamination of the control group in the event of a referral to the Department of Supportive Care, controls referred for psychosocial care will be seen, if possible, by therapists in the department who have not received prior training in CALM therapy (i.e., non-CALM-trained therapists). Contamination will be monitored and documented and is defined as having two or more sessions with a CALM-trained therapist.

### Treatment integrity

The treatment integrity of the intervention arm is ensured by means of weekly group supervision of therapists with case presentations. CALM sessions are audio-recorded, and therapists document sessions in a written report. Senior clinicians (GR, SH) assess overall and topic-specific competencies using treatment integrity rating scales adapted from Spiegel and Spira’s [18] tools. Evaluations are discussed with each therapist to improve competencies.

### Randomization

Permuted block randomization is used to allocate participants to a trial condition with stratification by PHQ-9 score (< or ≥ 10). Stratification ensures that highly depressed individuals will be balanced in both arms. The randomization process is managed by the Department of Biostatistics at the Princess Margaret Cancer Centre, which is independent of the trial team.

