The Posttraumatic Growth Inventory (PTGI) [46–48], a 21-item self-report scale that measures positive psychological changes after trauma, has been used as a measure of psychological growth in response to the psychological trauma of cancer [49] and as an outcome measure for intervention studies [50, 51]. The PTGI provides a total score based on the experience of new possibilities and spiritual change, growth in personal strength, relations with others, and appreciation of life.

The Quality of Life at the End of Life-Cancer Scale (QUAL-EC) [52] is a measure of quality of life in patient populations near the end of life. We omitted the symptom control subscale, thereby reducing this self-report measure to 14 items.

Death anxiety is assessed using the 15-item Death and Dying Distress Scale (DADDS), which we have developed for use in advanced cancer [53]. Unlike other death anxiety measures (e.g., [54]), the DADDS is designed for populations facing imminent death. It addresses fears about the dying process, and about lost opportunities and self-perceived burden placed on others as a result of impending mortality.

The Demoralization Scale (DS) [55] is a 24-item self-report measure that assesses loss of meaning and purpose, disheartenment, and helplessness.

Attachment security is assessed using the 16-item modified Experiences in Close Relationships Inventory (ECR-M16) [56], tailored for use with advanced cancer patients. It assesses attachment avoidance (i.e., discomfort with closeness and discomfort depending on others) and attachment anxiety (i.e., fear of rejection or abandonment).

Participants who are married, common-law, or in a long-term relationship will be asked to complete the ten-item Couple Communication Scale (CCS) [57], which is concerned with an individual’s feelings, beliefs, and attitudes about the communication in his/her relationship; the CCS is taken from the PREPARE/ENRICH Inventory [57].

Lastly, the Clinical Evaluation Questionnaire (CEQ) is a seven-item measure that we have newly developed to assess the extent to which individuals feel emotionally supported by clinical services in the domains relevant to CALM therapy. For intervention participants, the CEQ refers to the patients’ experience of CALM therapy. For control participants, the CEQ refers to the patient’s interactions with the health care team at the Princess Margaret. The CEQ is assessed only at 3 and 6 months. See Additional file 1 for this measure.

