### Proposed analyses

Analyses will be by intention to treat. ANCOVA will be used to test for outcome differences between experimental and control groups at follow-up, controlling for baseline scores and covariates, specifically age, gender and symptom burden from disease. Sensitivity analyses, including complete case analysis and multiple imputation, will be conducted to assess the impact of missing values. Linear mixed effects modeling will be used to test for group differences in trajectory over time. Intervention participants are expected to show greater benefit (i.e., less distress or greater well-being) over time relative to control participants. Structural equation modeling and factor analysis may also be used to study treatment effects on combined or composite outcomes.

The outcome of death anxiety may require special consideration, since death anxiety scores at baseline in the very low range can represent minimization or non-reflectiveness about such concerns (unpublished observations). Non-reflective individuals may increase in death anxiety as their disease progresses and as avoidant psychological strategies become less effective with physical decline. Analyses will, therefore, examine the effect of removing individuals with low death anxiety scores at baseline (i.e., DADDS < 15). Effective psychotherapeutic intervention may actually be associated with increased death anxiety due to the processing of such concerns, thereby weakening the power to detect significant treatment effects.

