## Discussion

CALM therapy is a novel psychotherapeutic intervention that we have developed to alleviate distress and to promote psychological growth and well-being in patients with advanced or metastatic cancer. Unique features of this supportive-expressive therapy include its theoretical foundation in relational, attachment and existential theory, its tailored focus on the problems of advanced cancer, the inclusion of primary informal caregivers in one or more sessions of the intervention, and the potential for recruitment of participants from a clinic-based population. Although depression is specified as the primary outcome, we also place great importance on the secondary outcome measures, which we believe are highly relevant to the problem of advanced cancer and may be improved by the intervention.

There are particular challenges in an RCT of this kind. These include the identification of participants motivated to engage in psychotherapy at the time of recruitment, recruitment and retention of patients with advanced illness, and the possibility that outcomes will be affected by dramatic changes in clinical status that may occur during the course of advanced cancer. The clinic-based recruitment strategy is facilitated by the engagement of the research team with the oncology clinic staff. This clinic-based approach will be of great value to inform our understanding of the benefit of CALM in both depressed and non-depressed individuals who were not necessarily seeking professional psychosocial care.

We are fortunate to have recruited a group of committed and experienced psychosocial clinicians, who have been intensively trained and supervised to deliver the CALM intervention. Preliminary qualitative [4] and quantitative pilot studies [65] have provided support for the feasibility and value of CALM therapy, but the large phase III RCT described here will provide a more definitive assessment of its potential efficacy. Such evidence will determine whether it can be justified to routinely incorporate CALM into the comprehensive care of patients with advanced cancer.

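### The named ANCOVA covariates omit the PHQ-9 randomisation stratum, so tests of the non-PHQ-9 outcomes are slightly conservative; the primary analysis is essentially unaffected

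*Protocol article*

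**What the plan says.** Randomization section: "Permuted block randomization is used to allocate participants to a trial condition with stratification by PHQ-9 score", with the cut at 10. The only reason given is balance: "Stratification ensures that highly depressed individuals will be balanced in both arms".

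Proposed analyses section: the groups are compared at follow-up by ANCOVA, "controlling for baseline scores and covariates, specifically age, gender and symptom burden from disease". The PHQ-9 stratum is not named. For the longitudinal analysis the article says only: "Linear mixed effects modeling will be used to test for group differences in trajectory over time". No covariates are listed for that model.

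Outcome measures section: the primary outcome is the PHQ-9 itself. Most secondary outcomes are other scales with their own baseline score. The exception is the Clinical Evaluation Questionnaire: "The CEQ is assessed only at 3 and 6 months".

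**The concern.** Stratified blocking forces the arms to be alike on the stratifier. That removes the stratum's contribution from the true variance of the treatment contrast. A model without the stratum, or a close stand-in for it, leaves that contribution in the residual and reports a standard error larger than the true one. The estimate is not biased, but the test is conservative and the interval a little wide.

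The article does not leave its covariates open. It names them, and the one factor built into the allocation is missing. If baseline scores means each outcome's own baseline, then the models for GAD-7, FACIT-Sp, DADDS, the Demoralization Scale, PTGI, QUAL-EC and the rest carry neither the stratum nor baseline PHQ-9. The CEQ model does not even have an own baseline to absorb part of it. At stake is some precision on secondary outcomes that the Discussion says matter greatly to the investigators.

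**Working it through.** **Inputs from the article.** Two-sided alpha 0.05 (z = 1.96), power 0.80 (z = 0.842), d = 0.405, recalculated baseline-to-6-month correlation 0.50, completion 75%, compliance 90%.

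**Assumptions, not in the article.** Share with PHQ-9 of 10 or more, block size, correlations between PHQ-9 and the other scales, and hence R², the share of residual outcome variance that the stratum explains given the other covariates.

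**1. The plan's own figure.** n = 2(1.96 + 0.842)²(1 − 0.50²)/0.405² + 1 = 72.8, so 73 per group at study end. At baseline, 73/(0.75 × 0.90²) = 120.2, so 121 per group and 242 in all. This reproduces the article. The formula has no stratum term, so the sample size does not depend on this point.

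**2. Size and power as a function of R².** Without the stratum, the reported standard error exceeds the true one by the factor 1/√(1 − R²). The true two-sided size is 2[1 − Φ(1.96/√(1 − R²))].

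For power at 73 per group, the residual SD is √(1 − 0.50²) = 0.866, and the reported SE is 0.866 × √(2/73) = 0.14335.
- Without the stratum: Φ[(0.405 − 1.96 × 0.14335)/(0.14335√(1 − R²))]
- With it: Φ[0.405/(0.14335√(1 − R²)) − 1.96]

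Example, R² = 0.10: the true SE is 0.14335 × 0.9487 = 0.1360. Without the stratum, 0.1240/0.1360 = 0.912 gives 0.819. With it, 2.978 − 1.96 = 1.018 gives 0.846.

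| Assumed R² | SE too large by | True size | Power without | Power with |
|---|---|---|---|---|
| 0.01 | 0.5% | 0.049 | 0.808 | 0.810 |
| 0.02 | 1.0% | 0.048 | 0.809 | 0.814 |
| 0.05 | 2.6% | 0.044 | 0.813 | 0.826 |
| 0.10 | 5.4% | 0.039 | 0.819 | 0.846 |

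**3. Simulation.** 182 completers (242 × 0.75 = 181.5), blocks of 4, 30% with PHQ-9 of 10 or more, and a true effect of 0.405 SD for power. There were 8,000 trials for size (simulation error about √(0.05 × 0.95/8000) = 0.0024) and 3,000 for power. Age, gender and symptom burden were not included.

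| Setting (assumed correlations) | R² | Size without / with | Power without / with |
|---|---|---|---|
| Primary PHQ-9, baseline r 0.5 | 0.000 | 0.047 / 0.048 | 0.885 / 0.885 |
| Own baseline 0.5; PHQ-9 with own baseline 0.5, with outcome 0.35 | 0.009 | 0.046 / 0.048 | 0.885 / 0.886 |
| Own baseline 0.6; PHQ-9 with own baseline 0.6, with outcome 0.45 | 0.009 | 0.048 / 0.049 | 0.922 / 0.923 |
| Own baseline 0.5; PHQ-9 with own baseline 0.3, with outcome 0.4 | 0.050 | 0.0455 / 0.050 | 0.886 / 0.895 |
| CEQ, no baseline; PHQ-9 with outcome 0.2 | 0.023 | 0.047 / 0.051 | 0.764 / 0.771 |
| CEQ, no baseline; PHQ-9 with outcome 0.4 | 0.092 | 0.041 / 0.050 | 0.792 / 0.818 |

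**4. Reading the two together.** The primary analysis gains nothing from the stratum. Outcomes with an own baseline gain at most about 1 point of power in the simulation. The CEQ gains about 1 to 3 points.

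**The case against.** The best defence is that this is a small effect in the safe direction, on secondary outcomes only, and that the covariates of secondary models are routine detail for an analysis plan that is not shown. Symptom burden is also a planned covariate. The Background lists the physical burden of disease among the main contributors to depressive symptoms, so it would take up part of what the stratum explains; the simulation leaves it out and so leans high. The simulation also blocks the completers directly, whereas dropout would break some blocks and bring the size nearer to 0.05. Finally, baseline scores could be read to include baseline PHQ-9 in every model.

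Most of this stands and sets the size of the point. It does not remove it, because the article chose to name its covariates and the named set leaves out the stratifier. If baseline PHQ-9 was meant for every model, saying so resolves the point.

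A reader might go further in two ways.

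- **That no analysis accounts for the stratifier, so the primary test suffers.** It does not: the primary ANCOVA adjusts for continuous baseline PHQ-9.
- **That the article promises separate evidence for depressed and non-depressed patients and then plans none.** The words in the Discussion, "benefit of CALM in both depressed and non-depressed individuals who were not necessarily seeking professional psychosocial care", describe what recruiting in clinics can inform. They are not an objective, a hypothesis or a planned analysis, and the Randomization section gives balance as the only purpose of stratifying. Subgroup and interaction tests are commonly left to the analysis plan. Such a test would also be weak: with 146 to 182 completers and an assumed 20% to 40% at PHQ-9 of 10 or more, power for a between-stratum difference of 0.405 is 0.20 to 0.34.

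**Conclusion.** The point holds in a limited form, with minor severity. Followed as written, the ANCOVA leaves a balanced prognostic factor in the residual for the non-PHQ-9 outcomes. For R² between 0.01 and 0.10, the true size is about 0.049 to 0.039 instead of 0.05, and the power loss is about 0 to 3 points. The upper end is plausible mainly for the CEQ. A larger loss needs a larger R² (at 0.20 the size would be 0.028), and nothing in the article supports one.

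There is no type I error inflation, no bias in the treatment effect, no material effect on the primary analysis and no change to the 242. The figures rest on assumed correlations, stratum share and block size, and apply to continuous scores analysed by ANCOVA; the SCID diagnosis is not covered by them. The article names no covariates for the mixed models, so nothing is misstated there, but the same term belongs in them.

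**What to change.** Under Proposed analyses, add the PHQ-9 stratum, or continuous baseline PHQ-9, to the covariates of every model for an outcome other than the PHQ-9. Name the CEQ explicitly, since it has no baseline score, and state that the mixed models carry the same term. State also that the primary model's baseline score is the continuous PHQ-9, so that it is clear the stratifier is already covered there.

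The cost is one sentence and one degree of freedom per model. The stratum is recorded at randomisation and baseline PHQ-9 is already collected, so no new data are needed and the sample size is unchanged.
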